### COVID-19 Adaptations

Assessments and interventions were initially designed to be conducted face-to-face. In response to the COVID-19 pandemic, local lockdowns, reduction in nonurgent face-to-face health care, and cancellation of nonurgent elective surgery with decreased surgery activity, face-to-face recruitment, and intervention delivery were paused in March 2020. The study protocol was adapted to use digital technologies and telehealth methods, and recruitment was recommenced in August 2020. Textbox 2 highlights the key changes.

Protocol telehealth adaptations to accommodate the COVID-19 pandemic.Inclusion criteriaAccess to internet-based videoconferencing platforms including email address and internet (family members to assist if required)ConsentElectronically completed consent formsBaseline, before surgery, and 30 days after surgery assessmentsAssessments conducted remotely over videoconferencing or zoom appointments with links emailed to participantsNutrition assessmentAnthropometric variables self-measured: weight, height, and girths (waist, hip, and midarm; standardized tape measure provided)Body composition analysis omittedExercise assessmentRemote functional capacity assessment6-minute walk test and hand grip test omittedContinuation of 30-second chair stand, 2-minute step test, 3-m timed up and go (to measure cardiovascular fitness)Supervised exercise interventionHome-based individualized supervised exercise sessions conducted remotely via videoconferencing or zoomPrinciples of the original protocol were followed in terms of frequency, intensity, time, and types of exerciseNutrition interventionEducation material and high protein oral nutritional supplements mailed to participantsPatient-reported outcome questionnairesCompleted by hard copy (mailed out) or web-based or electronically using Research Electronic Data Capture

### Statistical Analysis

#### Sample Size

The sample size is pragmatic, which is based on 2018/2019 surgical and oncology site numbers. We estimate that 50% (n=85) of eligible participants will agree to participate in the prehabilitation program. The study anticipates recruiting 100 participants over a 12-month period. Based on our pilot study adherence and the short-term nature of the intervention, we anticipate attrition will be less than 20% (n=20) of those who complete the baseline assessment, but higher in those who have already undergone neoadjuvant chemotherapy. This gives us sufficient statistical power at the 5% significance level to detect an increase of 20 m in the distance walked in the 6MWT from baseline to postintervention based on our pilot study.

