In the past decade, the focus of optimizing patients in the preoperative period to withstand the upcoming surgical stressor has emerged in a concept known as prehabilitation. Prehabilitation aims to improve preoperative functional reserves through physical, nutritional, and psychological interventions to mitigate the predictable detrimental effects of surgery [11,12]. While early prehabilitation studies focused on the feasibility of singular interventions [12], a multimodal (exercise, nutrition intervention, and psychological support) approach is increasingly favored [13-17]. We previously reported a pilot feasibility study of a short-term multimodal (exercise, healthy eating, and nursing support) prehabilitation program in CRC surgery [18]. In total, 22 participants completed the program, and the median length of the intervention was 14 (range 7-29) days. We found that attendance was excellent (78.5%, mean 3.5 sessions), moderate-intensity aerobic exercise increased from 17 to 73 minutes per week, and functional capacity measured using the 6-minute walk test (6MWT) [19,20] had a clinically significant increase of 48 (from 435 to 483) m. Participant satisfaction was excellent, with all participants strongly recommending prehabilitation.

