## Methods

### Study Design and Setting

This protocol describes a translational, implementation study that will investigate a multimodal prehabilitation intervention, in a nonblinded, nonrandomized, single-group, pre-post design, in patients with colorectal cancer and upper gastrointestinal cancer undergoing potentially curative intent surgery at Concord Repatriation General Hospital, a tertiary teaching hospital in Sydney, Australia. The study will be evaluated using the RE-AIM Evaluation framework [22,23] (Table 1). Exploratory comparisons of some secondary end points will be made with historical colorectal cancer and upper gastrointestinal patient data obtained from the hospital’s surgical database. The minimum recruitment period will be 12 months. Recruitment commenced in January 2020.

**Table 1 table1:** Reach, Effectiveness, Adoption, Implementation, and Maintenance evaluation framework adapted to prehabilitation before gastrointestinal cancer surgery study.

Domain	Description	Data collection instrument
Reach	The number (and proportion) of eligible patients having gastrointestinal cancer surgery who participated (numerator) and how representative they are of the target population (denominator) of participants and eligible patients who did not consent Participant characteristics and comparison to nonparticipants	Patient screening logs Prehabilitation before gastrointestinal cancer surgery study Research Electronic Data Capture (Vanderbilt University) database including demographics
Effectiveness	Changes in functionality, nutrition, and well-being from pre- to post intervention	Participant-reported outcomes (psychological status, and quality of life) and functional assessments (6-minute walk test and 2-minute step test), nutritional status, and body composition, at baseline, before surgery, and 30 days after surgery assessments
Adoption	For the single site, the number of surgeons who participated versus invited surgeons, characteristics of participating surgeons versus non-participating surgeons, the number of referrals received, referral sources, and barriers to referrals Clinician and surgeon perceptions	Number of referring surgeons (numerator) versus total number of surgeons at the site treating colorectal cancer or upper gastrointestinal cancer patients (denominator) In-house clinician satisfaction surveys

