## Results

The study recruitment commenced in January 2020. Recruitment was paused in March 2020, due to the COVID-19 pandemic, and the protocol was adapted to include a remote or telehealth intervention. Recruitment restarted with the telehealth adaptations in August 2020. Due to ongoing COVID-19 disruptions (restrictions and cancellation of elective surgeries at the hospital), recruitment was extended until December 31, 2021. During the 16-month active recruitment period, a total of 198 (133 CRC and 65 UGI) patients were screened, of which 102 were ineligible. The most common reasons for ineligibility were less than a 14-day intervention time period between screening or referral and scheduled surgery date (n=64), not for surgical intervention (n=12), and not medically cleared to exercise (n=6). In total, 96 patients met the eligibility criteria, and 77 were recruited (64 patients with colorectal cancer and 13 patients with upper gastrointestinal cancer). The results from the study will be analyzed and published in a peer-reviewed journal.

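### The only power statement rests on about 80 paired 6-minute walk tests, but the telehealth adaptation omits that test, so the statement is unsupported for the study as adapted

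*Protocol article*

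**What the plan says.** The Sample Size section describes the number as pragmatic, taken from 2018/2019 site volumes. It then says "The study anticipates recruiting 100 participants over a 12-month period" and "we anticipate attrition will be less than 20% (n=20) of those who complete the baseline assessment". From these it concludes that the study has "sufficient statistical power at the 5% significance level to detect an increase of 20 m in the distance walked in the 6MWT", measured from baseline to postintervention and with the pilot as its source. It gives no numerical power, no SD of change and no sidedness. The Introduction gives only the pilot's mean change: among 22 completers the 6MWT "had a clinically significant increase of 48 (from 435 to 483) m".

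The COVID-19 Adaptations textbox moves all three assessments to videoconferencing. Under remote functional assessment it drops the 6MWT and handgrip, and keeps the 30-second chair stand, the 2-minute step test and the timed up and go. The Results section says that recruitment paused in March 2020, that "Recruitment restarted with the telehealth adaptations in August 2020", and that it closed on 31 December 2021 with 77 recruited.

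The Effectiveness row of Table 1 still lists "functional assessments (6-minute walk test and 2-minute step test" at all three assessments, and Table 2 still lists the 6MWT. Neither table says that it applies to face-to-face assessment only.

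**The concern.** The article presents the protocol together with its pandemic adaptations and reports final recruitment, yet the power statement describes the study before either. Its basis is about 80 people walking the test twice. The adapted protocol does not collect the test remotely, and the total recruited is below 80 before any attrition.

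The planned mixed models include everyone with baseline data. For the 6MWT, a participant assessed only remotely has no baseline value and cannot contribute. A reader who relies on the Sample Size section could take a null 6MWT result as adequately powered evidence of no gain, or a positive one as describing the whole program. Either result would probably come from a small early face-to-face subset.

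**Working it through.** **Inputs from the article.** Target change 20 m; significance level 5% (two-sided assumed); planned N 100; attrition 20%; 77 recruited; face-to-face recruitment from January to March 2020, taken as 2 to 3 months; 16 months of active recruitment reported.

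**Assumed, because not given.** The SD of the within-person 6MWT change (30 to 60 m shown), and that only participants enrolled before the pause have a 6MWT.

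**Method.** Paired t-test with noncentrality (20 / SD) × √n on n − 1 degrees of freedom, two-sided 5%.

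**Step 1: the stated claim.** Pairs = 100 − 20 = 80. By the normal approximation, the largest SD giving 80% power is 20 × √80 / (1.960 + 0.842) = 63.9 m; the exact t calculation gives 63.1 m. For 90% power the limits are 55.2 m and 54.5 m. At SD 50 m, 80 pairs give 94%. The claim cannot be reproduced exactly without an SD, but it was plausible for the original design.

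**Step 2: pairs left after the adaptation.**
- Achieved rate, 77 over 16 months: 77 × 2/16 = 9.6 to 77 × 3/16 = 14.4 enrolled before the pause.
- August 2020 to December 2021 alone spans 17 calendar months, so the 16 months may exclude further pauses. Over 19 or 20 months the figures are 77 × 2/19 = 8.1 and 77 × 3/20 = 11.6.
- Achieved rate overall: about 8 to 14 enrolled. Times 0.8: about 6 to 12 pairs.
- Planned rate, 100 over 12 months: 16.7 to 25 enrolled. Times 0.8: about 13 to 20 pairs.

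The share of the 77 without a 6MWT is then about 81% to 90% at the achieved rate and 68% to 78% at the planned rate.

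**Step 3: power for 20 m.**

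| Pairs | SD 30 m | SD 40 m | SD 50 m | SD 60 m |
|---|---|---|---|---|
| 80 (as stated) | >99% | 99% | 94% | 84% |
| 61 (77 less 20%, had all been tested) | >99% | 97% | 87% | 73% |
| 20 | 81% | 56% | 40% | 29% |
| 12 | 56% | 35% | 24% | 18% |
| 6 | 27% | 17% | 13% | 10% |

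Pairs needed for 80% power are 20, 34, 52 and 73 at SD 30, 40, 50 and 60 m.

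**Step 4: a test kept in both modes.** 77 × 0.8 = 61.6, so about 62 pairs. These give 80% power for a mean change of about 0.36 SD.

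**The case against.** The strongest defence is that little depends on the sentence. The sample size was set by site volume, not by the 6MWT. The RE-AIM primary outcome is to be reported descriptively. The 6MWT is one of six functional assessments in Table 2, the article discloses its omission openly, and the 2-minute step test already serves the Effectiveness domain in both modes. All of this stands, and it limits the importance of the point. It does not make the power statement right for the adapted study.

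A reader might go further and infer that the claim is simply false, or that almost all participants lack the test. The documents do not establish either. They do not say how many of the 77 enrolled before the pause, how many had a 6MWT, or whether any in-person assessment resumed later, and the Conclusions speak of delivery face-to-face or by telehealth. The split is inferred from dates and an assumed constant rate, which supports most but not almost all. With the SD also unknown, one favourable corner (20 pairs, SD 30 m) still reaches about 81%.

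Nor is there an arithmetic error in the original plan: 80 pairs would have been enough for any SD up to about 63 m. The fault is a planning statement left unrevised after the adaptation.

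**Conclusion.** The Sample Size section and the COVID-19 Adaptations section are inconsistent. The stated basis of about 80 6MWT pairs cannot hold, since only 77 people were recruited and the test was dropped from remote assessment. The power statement is unsupported and very probably untrue for the study as adapted.

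The size rests on three assumptions: only January to March 2020 enrollees have the test, attrition is 20%, and the SD of change lies between 30 and 60 m. On these, 80% power is reached only at the most favourable edge. If in-person testing resumed after August 2020, there would be more pairs; if the pause cost early enrollees their presurgery walk, fewer. Importance is moderate: no primary test or decision depends on the 6MWT, but this is the document's only power statement.

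**What to change.** - Withdraw the 20 m power sentence, or label it as describing the design before the telehealth adaptation.
- Report the number of participants with paired 6MWT data, and present the 6MWT change as a face-to-face subset result.
- Mark the 6MWT in Tables 1 and 2 as face-to-face only.
- State precision for a functional test kept in both modes, for example the 2-minute step test already in Table 1: about 62 pairs give 80% power for about 0.36 SD of change. It need not become the sole functional measure.

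The cost is a change of wording in one section and two tables, and a less favourable stated sensitivity. No new data are needed, and neither the sample nor the descriptive primary analysis changes.

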#### Statistical Analyses

The primary outcome based on the RE-AIM evaluation framework will be reported descriptively, with a focus on referral, recruitment, and retention targets.

Secondary end points including baseline characteristics, functional, and nutritional status, will be reported using descriptive statistics, mean (SD) for normally distributed data, or median and IQR for nonnormally distributed data. Counts and percentages will also be used as appropriate. Reported changes in outcome variables from baseline to postintervention (presurgery) and 30 days after surgery will be measured using mixed models and will include all participants with baseline data including those with missing data at follow-up, with adjustment for predictors of dropouts to minimize selection bias. Postsurgery outcome variables will be evaluated using mixed models. Outcomes for UGI cancer and CRC participants will be evaluated separately and combined. Length of hospital stay and postsurgical complications will be compared to historical data from the hospital’s surgical 2019 database.

Responses to the investigator-developed questionnaire (participants and clinician) will be presented descriptively using means (SDs) or medians (IQR) and counts and percentages as appropriate. Free text responses will be summarized. The statistical package SPSS (version 24 or the newest release) will be used for quantitative data analysis.

Semistructured interviews regarding participant satisfaction will be transcribed verbatim and undergo qualitative content analysis. Initial transcript sample readings will be carried out. Themes and content will be analyzed descriptively. Coding, linking, and retrieving the qualitative data will be conducted using NVivo software (QSR International).

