While the evidence surrounding prehabilitation grows, how it transitions from a trial setting to being integrated into a real-world health setting is less clear. Implementation science frameworks aim to help understand the barriers and facilitators to support the uptake of research findings into routine clinical care [21]. The “RE-AIM” (Reach, Effectiveness, Adoption, Implementation, Maintenance) evaluation framework [22,23] is a theoretical implementation framework that can guide and assess the translation from research into practice at both the individual and organizational levels. The primary aim of this study is to evaluate the implementation of a multimodal (supervised exercise, nutrition intervention, and nursing support) prehabilitation program into standard care for patients with gastrointestinal cancer (CRC and UGI cancer) scheduled for curative intent surgery using the RE-AIM framework. The secondary aim is to determine the impact of a multimodal prehabilitation program on functional capacity, nutritional and psychological status, quality of life (QOL), length of stay at the hospital, and postsurgical outcomes including complications and recovery. We hypothesize that prehabilitation (1) will be feasible, with good participant adherence; (2) will decrease the length of stay at the hospital and postsurgery complications; and (3) improve functional and nutritional status, recovery, and QOL. Here, we outline the trial protocol, including adaptations made to accommodate the COVID-19 pandemic.

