### Study Population

Patients will be considered eligible if they are 18 years or older, undergoing elective colorectal cancer or upper gastrointestinal cancer resection with curative intent at the Concord Repatriation General Hospital with a minimum of 14 days prior to surgery for the intervention. All participants must be medically fit to exercise as determined by their treating physician, willing to attend supervised exercise sessions at the Sydney Cancer Survivorship Gym Concord Repatriation General Hospital 1-2 times per week, take prescribed high protein oral nutritional supplements, and have Eastern Co-operative Oncology Group performance status of 0-2 [24]. Patients treated with neoadjuvant chemotherapy or radiotherapy are eligible to participate after completion of neoadjuvant chemotherapy or radiotherapy provided there is a 14-day intervention time available before surgery. Patients who do not speak English are eligible and will be provided with a professional health interpreter. Inclusion and exclusion criteria are further outlined in Textbox 1.

Study inclusion and exclusion criteria.

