## Discussion

### Principal Findings

Surgery remains the standard curative treatment for early-stage CRC and UGI cancers. Despite advancements in surgical practices and postoperative care pathways, morbidity and mortality rates remain high [6,7,10]. A reduction in postoperative complications is important. It is well established that the number and severity of postoperative complications are associated with preoperative health status, functional capacity, nutritional status, and muscle strength [44]. While traditional approaches have focused on lifestyle modifications in the postoperative period, recent evidence shows that the preoperative period may be the more appropriate time to intervene [45].

Positive lifestyle practices, including exercise and nutrition, are associated with many health benefits and have been shown to decrease the risk of several common cancers, including CRC and some UGI cancers, and possibly to decrease the risk of cancer recurrence [46,47]. However, only approximately 20% of people diagnosed with cancer are meeting the current exercise guidelines [48-50], and only 37% of patients with gastrointestinal cancer undergo nutrition screening and are offered preoperative nutrition support [51,52]. Recent reviews indicate that optimizing functional capacity with exercise, nutrition interventions, and psychological support strategies in a gastrointestinal surgical population resulted in reduced complications, length of hospital stay, and improved QOL [13-17]. However, few studies have evaluated the integration of prehabilitation practices into standard of care.

This pragmatic prehabilitation program will deliver integrated care, increasing patients’ self-management skills to support healthy living during and after a cancer diagnosis. It has the potential to change standard care with a simple, safe, relatively inexpensive coordinated intervention that confers multiple physical and psychological health benefits. This study will determine whether a multimodal (exercise, nutrition intervention, and nursing support) prehabilitation program can be integrated into routine standard care and whether it improves outcomes by reducing postoperative complication rates and length of stay at the hospital. Unique data will be collected on physical activity, nutritional status, dietary intake, and psychological well-being and their influence on surgical outcomes to inform the current evidence base in gastrointestinal surgical oncology preoperative care.

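### The historical comparison of stay and complications with 2019 has no stated eligibility restriction or adjustment and cannot bear the Discussion's claim to determine the program's effect

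*Protocol article*

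**What the plan says.** The design is a "nonblinded, nonrandomized, single-group, pre-post design" (Study Design and Setting), so there is no concurrent control. The same section states: "Exploratory comparisons of some secondary end points will be made with historical colorectal cancer and upper gastrointestinal patient data". Under Statistical Analyses the comparator is fixed: "Length of hospital stay and postsurgical complications will be compared to historical data" from the 2019 surgical database. The sentence before it has CRC and UGI outcomes evaluated both separately and combined. The only adjustment named in that paragraph is for predictors of dropout, and it belongs to the mixed models of change from baseline.

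Two other places give this contrast more weight. The Introduction hypothesises that prehabilitation "will decrease the length of stay at the hospital and postsurgery complications". The Discussion (Principal Findings) says the study will determine "whether it improves outcomes by reducing postoperative complication rates and length of stay at the hospital".

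Participants had to have at least 14 days before elective surgery, medical clearance to exercise, an ECOG "performance status of 0-2", and to consent (Study Population and Textbox 1). After the pandemic adaptations they also needed internet access (Textbox 2). The Results section reports that "a total of 198 (133 CRC and 65 UGI) patients were screened, of which 102 were ineligible" and then "In total, 96 patients met the eligibility criteria, and 77 were recruited (64 patients with colorectal cancer and 13 patients with upper gastrointestinal cancer").

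**The concern.** A group filtered on fitness, time to surgery and willingness is set against a calendar-year surgical database with no stated filter. The Discussion itself calls it well established that complications track preoperative health status and functional capacity, and exercise clearance and performance status select on exactly those. The Introduction singles out UGI cancer for high morbidity, and UGI patients are under-represented among participants relative to those screened. Both differences lean towards the program.

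Calendar time differs as well. The comparator year is pre-pandemic, whereas recruitment ran through cancellations of elective surgery.

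With a single-group design, no other between-group evidence bears on the second hypothesis. A favourable difference would be read through the Discussion's wording as showing that the program reduces complications and stay, although the contrast cannot separate the program from selection, case mix and period.

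**Working it through.** The plan gives no sample size, effect size or power for this comparison, so there is no figure of its own to reproduce. The check asks how large an apparent benefit could be with no program effect.

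**Inputs from the Results section.** Screened 198 (133 CRC, 65 UGI); ineligible 102, of whom 64 had under 14 days, 12 were not for surgery, 6 were not cleared to exercise, and 102 − 64 − 12 − 6 = 20 had other reasons. Eligible 198 − 102 = 96; recruited 77 (64 CRC, 13 UGI). The counts agree with each other.

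**Assumptions.** Complication rates are 30% in lower-risk and 50% in higher-risk patients, the ends of the general range in the Introduction. The document does not give these as rates for eligible and ineligible patients. The 2019 mix is taken to equal the screened mix. The 19 eligible patients who were not recruited are given the participants' risk, so self-selection by consent is not counted.

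**Selection.** If a share f of the 2019 cohort is higher-risk, then

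2019 rate = 30% + f × (50% − 30%), and apparent reduction = f × 20 points.

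The 12 patients not for surgery would not be in a surgical database, so after the first row the denominator is 198 − 12 = 186. The last column is the chance of a significant result favouring the program under a two-sided 5% two-proportion z-test, with 77 participants and an assumed 170 to 340 historical patients. The plan names no test; the nominal chance in that direction is 2.5%.

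| Patients at 50% | f | 2019 rate | Apparent reduction | False benefit |
|---|---|---|---|---|
| All 102 ineligible | 102/198 = 51.5% | 40.3% | 10.3 points | 34-38% |
| Ineligible, without the 12 not for surgery | 90/186 = 48.4% | 39.7% | 9.7 points | 30-35% |
| Short interval plus not cleared | 70/186 = 37.6% | 37.5% | 7.5 points | 20-23% |
| Not cleared plus the 20 others | 26/186 = 14.0% | 32.8% | 2.8 points | 6-7% |
| Not cleared only | 6/186 = 3.2% | 30.6% | 0.6 points | 3% |

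Worked example, first row with 170 historical patients: pooled rate 0.371; null SE = √(0.371 × 0.629 × (1/77 + 1/170)) = 0.0664; SE under the gap = √(0.30 × 0.70/77 + 0.403 × 0.597/170) = 0.0644; Φ((0.103 − 1.96 × 0.0664)/0.0644) = 0.34.

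With assumed rates of 30% and 40%, every gap halves. The second row becomes 4.8 points, with an 11-12% chance of false benefit.

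**Tumour mix.** CRC share: 64/77 = 83.1% of participants, 133/198 = 67.2% of screened. UGI share: 13/77 = 16.9% against 65/198 = 32.8%, a difference of 0.1595. The apparent reduction in the combined result is 0.1595 × (UGI rate − CRC rate):
- CRC 30%, UGI 50%: 36.6% − 33.4% = 3.2 points.
- CRC 30%, UGI 40%, or CRC 40%, UGI 50%: 1.6 points.
- CRC 25%, UGI 50%: 4.0 points.

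For length of stay, if the mean for UGI exceeds that for CRC by an assumed 4 to 7 days, mix alone gives 0.1595 × 4 = 0.6 to 0.1595 × 7 = 1.1 days.

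The selection and mix illustrations may overlap, because some of the eligibility loss is itself among UGI patients. Their sizes should not simply be summed.

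**Status of the comparison.** Study Design and Setting makes it exploratory. Principal Findings has the study determine an effect on the same two outcomes, for which no other between-group comparison is planned. These two statements cannot both stand.

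**The case against.** The strongest reply is that this is one sentence in a condensed article. Rules for extracting the historical cohort and a covariate list are commonly left to a full protocol or analysis plan, and neither is shown. A reader might infer that the 2019 cohort is unrestricted and the analysis unadjusted. The document does not say so, and it does limit the historical data to CRC and UGI patients. That part of the reply stands: the most one can say is that no eligibility restriction or adjustment is stated. It does not remove the conflict between the exploratory label and the Discussion's claim, which no further detail elsewhere would resolve.

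Separate evaluation of CRC and UGI removes the difference in CRC/UGI share from the stratum results. This also stands. It leaves the combined result exposed, and it does not touch selection on interval, fitness or consent within a stratum.

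A reader might also infer that a spurious 10-point benefit is the expected outcome. The reasons for ineligibility do not support that. Of the 102, 64 were excluded on scheduling, and nothing in the document says that such patients carry 20 points more risk. If only the plausibly less fit do, the gap is 0.6 to about 3 points. Even the largest scenario gives a false benefit less often than not, so a false claim is possible rather than likely.

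Two further inferences fail. Pandemic-era change could bias the comparison either way, so it cannot be said to favour the program. Nothing shows that complications were graded differently in the 2019 database.

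Finally, the primary end point is the RE-AIM evaluation, reported descriptively, and this comparison is secondary. That limits the severity.

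**Conclusion.** The concern holds in a limited form. As written, the contrast sets a selected group against 2019 patients with no stated matching of eligibility and no adjustment. It is the sole between-group evidence on the second hypothesis and cannot deliver what the Discussion promises. With no program effect, selection could produce an apparent complication reduction of about 0.6 to 10 points, depending on which ineligible patients carry higher risk. Tumour mix could produce about 2 to 4 points, in the combined result only. These sizes rest on assumed complication rates and on the screened mix standing in for the 2019 mix, which is not given. The period effect is confounded with the program, with unknown sign. Severity is moderate.

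**What to change.** 1. Restrict the 2019 cohort to elective, curative-intent CRC and UGI resections that meet the study criteria as far as the database records them, including the interval of at least 14 days, performance status and no ongoing chemotherapy or radiotherapy. State which criteria cannot be applied.
2. Make the CRC and UGI strata the main historical comparison, or adjust the combined one for tumour site, procedure, age, comorbidity and neoadjuvant therapy. With 13 UGI participants, the UGI stratum will be imprecise and should be presented as such.
3. Use the same definitions of length of stay and Clavien-Dindo grade for both groups.
4. Reword Principal Findings as a hypothesis-generating statement that agrees with the exploratory label in Study Design and Setting.

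Concurrent non-participants from 2020-21 should serve at most as a descriptive check on calendar time. Of the 198 − 77 = 121 screened patients not recruited, 102 were ineligible, so as a comparator they would bring the selection problem back.

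The cost is extra extraction from a database already in use, a smaller historical cohort and a more modest claim. No new patients are needed. The article describes the results as still to be analysed, so the change can precede the analysis.
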